### 2.7 Statistical analysis

IBM SPSS software, release 29.0 (IBM Corporation, Armonk, New York, USA), R software version 4.3.2 (R Foundation for Statistical Computing, Vienna, Austria) and GraphPad Prism 10 (San Diego, California, USA) will be used for the data analyses. Descriptive statistics are used for the baseline demographic variables, primary and secondary outcomes. Continuous data is checked for significant outliers using studentized residuals and a normal distribution using the Shapiro Wilk Test, Q-Q plots, and histograms. Frequencies [number (N), %] are presented for counted (N falls, N adverse events if any, N of home exercises) and nominal data (gender, stroke etiology and location, and rehabilitation facility). Medians (interquartile range) are reported for ordinal data (mRS, BBS, FGA, TCT, FES-I, FRT, EQ-5D-3L, SARA, and SINGER), and mean (SD) is reported for continuous data (age, time after stroke, TUG, and posturography outcomes).

The significance level is defined by a two-tailed *p*-value of <0.05. Baseline (T0) between-group differences are evaluated using Fisher's exact test for nominal data, Mann Whitney-*U*-test for ordinal data and independent samples *t*-test for continuous data. If the distribution is non-normal in continuous data, data transformation or non-parametric statistics are performed, as appropriate. To evaluate within-group differences between T0, T1, and T2 measures, for ordinal data, Friedman test is utilized followed by Dunn's multiple comparisons test for pairwise comparisons. To examine between-group differences, using newly created variables (T1 or T2 minus T0 values), a Mann Whitney-*U*-test is performed. For continuous data, test assumptions for a repeated-measures analysis of variance (ANOVA) are checked (e.g., normality, sphericity) and dealt with as appropriate. If the requirements are met, repeated measures ANOVA are performed, with “time” (T0, T1, and T2 measurements) as the within-subject factor, “group” (IG, CG) as the between-subject factor, and adjusted for the stratification variables (age, sex). If statistical significance is present, a *post-hoc* analysis of pairwise comparisons between measurement time points is performed, followed by a *post-hoc* Bonferroni correction for multiple comparisons. An intention-to-treat analysis is performed analyzing all study participants in the groups which they have been assigned to.

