#### 2.5.2 Secondary outcomes

Secondary outcomes are static balance, as assessed using posturography (Tymo Balance Plate, Tyromotion, Austria), dynamic balance during walking, measured using the Functional Gait Assessment (FGA; Thieme et al., 2009), and trunk control, as assessed using the Trunk Control Test (TCT; Collin and Wade, 1990). Additionally, concerns about falling are assessed through the Falls Efficacy Scale International (FES-I; Yardley et al., 2005; Kempen et al., 2007), and risk of falling is determined according to the Functional Reach Test (FRT; Duncan et al., 1990, 1992). The number of falls is documented as well.

Further secondary outcomes include walking ability, evaluated using the Functional Ambulation Categories (FAC; Collen et al., 1990), functional mobility, as measured by the Timed Up and Go Test (TUG; Podsiadlo and Richardson, 1991), health-related quality of life, assessed utilizing the EuroQol questionnaire EQ-5D-3L (Rabin and de Charro, 2001; Greiner et al., 2005), severity of ataxic symptoms, as determined by the Scale for the Assessment and Rating of Ataxia (SARA), and patients' independence in daily life, measured using the Scores of Independence for Neurologic and Geriatric Rehabilitation (SINGER; Funke et al., 2009; Gerdes et al., 2012; Table 3).

Due to the time-point of study recruitment being a susceptible one for diminished physical and mental resilience (i.e., in the acute phase after stroke), FGA, EQ-5D-3L, and SINGER are not performed at T0.

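### The Functional Reach Test is classed as ordinal and compared by an unadjusted rank test on change, which makes poor use of its T0 value

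*Protocol article*

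**What the plan says.** Section 2.7 sorts the variables by name into four lists.

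- Counted: "presented for counted (N falls, N adverse events if any, N of home exercises".
- Nominal: "nominal data (gender, stroke etiology and location, and rehabilitation facility".
- Ordinal: "Medians (interquartile range) are reported for ordinal data (mRS, BBS, FGA, TCT, FES-I, FRT, EQ-5D-3L, SARA, and SINGER".
- Continuous: "mean (SD) is reported for continuous data (age, time after stroke, TUG, and posturography outcomes".

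The class sets the analysis. For ordinal data the groups are compared on change: "using newly created variables (T1 or T2 minus T0 values), a Mann Whitney-*U*-test is performed". Continuous data that meet the assumptions go to a repeated-measures ANOVA, "adjusted for the stratification variables (age, sex"; non-normal continuous data may be transformed or analysed non-parametrically.

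On the role of FRT, section 2.5.2 says that "risk of falling is determined according to the Functional Reach Test". Table 3 has it as the single entry for risk of falling, measured at T0, T1 and T2. The same section names "walking ability, evaluated using the Functional Ambulation Categories" as a secondary outcome. FAC is also measured at all three visits, but section 2.7 names it in none of its lists.

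**The concern.** FRT, like the Timed Up and Go (TUG) and posturography, is a performance test, and its name points to a measurement and not a set of grades. TUG and posturography are classed as continuous and FRT is not. The result for FRT is a rank test on a change score. That test ignores the stratification variables, uses T0 only by subtraction, and gives no between-group difference in units of reach.

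Subtracting T0 is inefficient when the T0-T1 correlation is moderate, which is plausible in early recovery after stroke, because it carries the full noise of the baseline into the outcome. At stake is the precision of the one comparison labelled as risk of falling. The primary analysis of the Berg Balance Scale (BBS) and the sample size are not affected.

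**Working it through.** **1. The plan's own figure.** The documents give no planning figure for FRT. The arm size used below comes from section 2.6 and reproduces:

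- Difference: 17.33 − 13.67 = 3.66.
- Pooled SD: √((2.08² + 4.73²)/2) = 3.654; × 1.442 = 5.269.
- n per arm = 2 × (1.960 + 0.842)² × 5.269² / 3.66² = 32.5, so 33, as stated.

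**2. Assumptions for FRT.** Reach is recorded as a distance. The group effect at T1 is 0.5 SD, SD is equal at T0 and T1, and the data are bivariate normal with correlation ρ = 0.3, 0.5 or 0.7. There are 33 per arm, and the test is two-sided at 0.05. None of the FRT values comes from the documents.

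**3. Variance of each comparison, in units of the SD².**

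- Change score: 2(1 − ρ).
- T1 adjusted for T0: 1 − ρ².
- Ratio: 2/(1 + ρ) = 1.54 / 1.33 / 1.18.

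**4. Approximate power.** Power ≈ Φ(z − 1.96), with z = 0.5 × √(33/2) / √variance and √(33/2) = 4.062. For the rank test, z is multiplied by √(3/π) = 0.977, its large-sample efficiency with normal data. The simulated column is from 6,000 trials per setting.

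| Method | z (ρ = 0.3 / 0.5 / 0.7) | Formula power | Simulated power |
|---|---|---|---|
| Mann-Whitney on change | 1.68 / 1.98 / 2.56 | 0.39 / 0.51 / 0.73 | 0.37 / 0.50 / 0.70 |
| t-test on change | 1.72 / 2.03 / 2.62 | 0.40 / 0.53 / 0.75 | 0.39 / 0.52 / 0.72 |
| Regression on T0 | 2.13 / 2.35 / 2.84 | 0.57 / 0.65 / 0.81 | 0.55 / 0.63 / 0.79 |

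**5. Where the gain comes from (simulated column).** The total gain is 0.18 / 0.13 / 0.09. Ranking accounts for about 0.02 at each correlation. Replacing subtraction by a T0 covariate accounts for 0.16 / 0.11 / 0.07. No effect of age or sex was simulated; the documents give nothing from which to size one.

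**6. Would the plan's continuous route be enough?** That ANOVA treats T0 as one of the repeated measurements, not as a covariate. It was simulated with three visits, ρ = 0.5 to 0.7 and the standardised effect of the BBS plan (3.66/5.269 = 0.69 SD of change). The power figures were:

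- Mann-Whitney on change: 0.77 to 0.78.
- t-test on change: 0.79 to 0.80.
- ANOVA group-by-time term: 0.83.
- ANOVA group main effect: 0.12 to 0.62.

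Moving FRT to the other list would therefore not by itself deliver the gain in step 4.

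**7. Departures from normality.**

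- With a floor on the reach values, Mann-Whitney on change has 0.42 / 0.53 / 0.72 against 0.53 / 0.60 / 0.75 with T0 adjustment, so the gain shrinks but mostly holds.
- With strong skew and high correlation it can vanish (0.72 against 0.69).
- It can also reverse. I simulated lognormal data (log-SD 0.8, ρ set on the log scale, shift of 0.5 SD, 6,000 trials). Mann-Whitney on change had 0.67 / 0.78 / 0.93 and the untransformed regression 0.61 / 0.66 / 0.78. A regression of T1 ranks on T0 ranks had 0.93 / 0.96 / 0.99, so using T0 as a covariate still pays; the untransformed scale is what fails.

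**8. FAC.** Table 1, Table 3 and section 2.5.2 all carry it; the four lists in section 2.7 do not. Table 3 has two rows for walking, FAC and TUG, and only TUG is given a class by name.

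**The case against.** The strongest reply is that the ordinal label does little harm in itself. A rank test is valid for a distance, costs about 2 to 3 points of power with normal data and can win with skewed data. Section 2.7 would in any case allow a non-parametric test for a non-normal continuous outcome. Patients enter with a BBS of 47 or less and a modified Rankin score of up to 4, so some may be unable to do the test, and a floor is possible. All of this stands. The power gain belongs to the T0 covariate, which the article offers to no outcome. It also stands that the article gives no unit for FRT, and that its medians would be in whatever unit is recorded.

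Three stronger readings are tempting, and the documents do not support them.

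- A reader might infer that FAC is left without any analysis. Section 2.7 promises descriptive statistics for all secondary outcomes and assigns tests by data type, and a set of ambulation categories would naturally follow the ordinal rule. What is missing is an entry in a list, in an article that condenses a fuller protocol.
- A reader might infer that walking rests on TUG alone. Section 2.5.2 describes the Functional Gait Assessment as measuring dynamic balance in walking, and section 2.7 names it in the ordinal list.
- A reader might infer that FRT is the only fall-related outcome. It is the only one with the risk-of-falling label; concerns about falling and the number of falls are separate secondary outcomes.

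**Conclusion.** The point holds as an inexpensive improvement to one secondary outcome. The stated comparison for FRT uses the collected baseline poorly and omits the stratification variables. Under the assumptions in the working, adjusting for T0 raises power from about 0.37/0.50/0.70 to 0.55/0.63/0.79. The gain is largest when the T0-T1 correlation is low, smaller with a floor, and not assured on the untransformed scale with strong skew. The classification is probably wrong but not proven so, because recording as a distance is inferred from the test's name. The omission of FAC is editorial. Neither matter touches the primary analysis or the sample size.

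**What to change.** State the scale and unit of FRT and move it to the continuous list. Compare reach at T1, and likewise at T2, by a regression on group with T0 FRT, age group and sex as covariates, and report the adjusted difference with a 95% CI. Keep a rank-based analysis as a check if the data are strongly skewed or have a floor, preferably one that also uses T0 FRT. State in advance the value given to patients who cannot be tested; this is the one small downside. Add FAC to the ordinal list.

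The cost is two list entries and one model line, with no new data. The change should be dated before unblinding, so that neither choice can follow the results.

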However, there are also limitations to consider in this study. Firstly, the study is conducted in a rehabilitation setting where patients receive additional individualized therapies. These supplementary therapies could potentially influence the study results, making it challenging to exclusively attribute the observed effects to the specific intervention under investigation. Secondly, as the trial focuses on acute stroke patients who undergo rapid recovery, selecting a timely and appropriate balance assessment over the 3-month study period is challenging due to the potential ceiling effect. To address this concern, the researchers chose 47 points or fewer in BBS as an inclusion criterion to ensure the detection of significant changes from T0 to T1 (Stevenson, 2001) and included the FGA to demonstrate effects during the sub-acute stages (T1 to T2). This limitation is relatively minor since the primary objective of the study is to evaluate the impact of supervised therapy sessions from T0 to T1. Thirdly, the initial training of therapists conducting the interventions had to be performed online because of the COVID-19 pandemic. This adjustment in training methods may influence the delivery and consistency of the therapy sessions. However, therapists have the option to watch the recording of the training, whenever they feel it is necessary to refresh certain aspects.

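### For ordinal outcomes the only planned T1-to-T2 test is within each arm, and for the FGA, included to show T1-to-T2 effects, none of the planned between-arm variables exists

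*Protocol article*

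**What the plan says.** Section 2.7 of the protocol article sorts the outcomes by scale type. The ordinal group includes the primary outcome: "Medians (interquartile range) are reported for ordinal data (mRS, BBS, FGA, TCT, FES-I, FRT, EQ-5D-3L, SARA, and SINGER".

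This group gets two kinds of test:

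- **Within each arm:** "To evaluate within-group differences between T0, T1, and T2 measures, for ordinal data, Friedman test is utilized". Dunn's test then compares the visits in pairs. With three visits, one of the pairs is T1 against T2.
- **Between arms:** "To examine between-group differences, using newly created variables (T1 or T2 minus T0 values), a Mann Whitney-*U*-test is performed". Both variables are changes from T0. No T2-minus-T1 variable is defined.

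Continuous outcomes (TUG, posturography) are handled differently. If the assumptions hold, they get a repeated-measures ANOVA with time and group as factors.

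Three statements elsewhere bear on this:

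- Section 2.5.2 says that the FGA, EQ-5D-3L and SINGER are left out at T0 because of limited resilience in the acute phase. Tables 1 and 3 agree: these three have entries at T1 and T2 only.
- The Discussion, dealing with the BBS ceiling, says that the researchers "included the FGA to demonstrate effects during the sub-acute stages (T1 to T2").
- The Discussion describes the population as "acute stroke patients who undergo rapid recovery" and says that the primary objective concerns T0 to T1.

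**The concern.** A within-arm test asks whether patients in that arm changed. In acute stroke they will, whichever therapy they receive, so a small p-value says nothing about coordination exercises against standard physiotherapy. Only a comparison of the randomised arms does.

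For the first window this matters less, because a between-arm test stands beside the within-arm one. For T1 to T2 the ordinal outcomes have only the within-arm test. If that result is asked to support a sub-acute effect, the available pattern is an improvement that is significant in one arm and not in the other. That pattern is common when the arms are identical.

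It can also point the wrong way. The Discussion hypothesises faster recovery and acknowledges a ceiling. An arm that has gained more by T1 has less room to gain by T2, so the control arm could be the one with the significant late improvement.

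The FGA is where the plan and its purpose part company. It was chosen to show effects after T1, yet the between-arm rule for ordinal outcomes needs a T0 value that the FGA does not have.

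**Working it through.** **1. The plan's own figure.** Inputs from section 2.6: mean BBS change 17.33 (SD 2.08) and 13.67 (SD 4.73), SD multiplier 1.442, two-sided alpha 0.05, power 0.80.

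- Difference: 17.33 − 13.67 = 3.66.
- Pooled SD, equal weights: √((2.08² + 4.73²)/2) = 3.654; times 1.442 = 5.269.
- n per arm = 2 × (1.96 + 0.84)² × 5.269² / 3.66², which rounds up to 33, as stated.

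The sample size is not at issue. It supplies the n = 33 used below.

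**2. Within-arm change in BBS, control arm only.** Paired z = mean change / (SD/√n).

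- SD 4.73: 13.67 / (4.73/√33) = 16.6.
- SD inflated to 4.73 × 1.442 = 6.82: 13.67 / (6.82/√33) = 11.5.
- Even with n = 5 and the inflated SD, approximate power is Φ(13.67/(6.82/√5) − 1.96) = 0.994.

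In a simulation with identical arms (33 per arm, 1,000 runs per scenario, assumed baseline BBS mean 30 and SD 9, change 13.67 with SD 6.82), the Friedman test and the T0-T1 and T0-T2 Dunn pairs were significant in every run.

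**3. The T1-T2 pair.** The documents give no T1-to-T2 change, so a mean gain of 0 to 6 points with SD 4 is assumed. Let p be the chance that one arm's T1-T2 Dunn pair (adjusted for three pairs) is significant. With identical, independent arms, the chance of significance in exactly one arm is 2p(1−p). This exceeds 5% when p lies between (1 − √0.9)/2 = 2.6% and (1 + √0.9)/2 = 97.4%, and it peaks at 50%.

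| Assumed gain T1-T2 | p, BBS capped at 56 | 2p(1−p) | One arm only, simulated | p, no cap | One arm only, simulated, no cap |
|---|---|---|---|---|---|
| 0 | 0.0% | 0.0% | 0.0% | 0.1% | 0.1% |
| 1 | 0.2% | 0.4% | 0.4% | 0.7% | 1.4% |
| 2 | 2.9% | 5.6% | 5.4% | 9.3% | 17.5% |
| 3 | 18.6% | 30.3% | 28.6% | 41.8% | 49.4% |
| 4 | 50.8% | 50.0% | 51.2% | 81.0% | 32.6% |
| 6 | 94.5% | 10.4% | 10.1% | 99.7% | 0.5% |

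With a different assumed baseline (mean 32, SD 10, capped at 47), the one-arm-only rate was 0.1% to 2.4% at gains of 0 to 2, then 17%, 40%, 44% and 24% at gains of 3, 4, 5 and 6, and 4% at 8.

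**4. A between-arm T2-minus-T1 test, for comparison.** In the runs tabulated above, a Mann-Whitney test of T2 − T1 between identical arms rejected in 3.8% to 6.2% of trials, against a nominal 5%.

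**5. What can be computed for each outcome.**

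| Outcome | T1 − T0 between arms | T2 − T0 between arms | T1 to T2 between arms | Friedman over three visits |
|---|---|---|---|---|
| BBS and other ordinal outcomes with a T0 value | yes | yes | not defined | yes |
| FGA, EQ-5D-3L, SINGER | no T0 value | no T0 value | not defined | not as written |
| TUG, posturography | in the ANOVA | in the ANOVA | in the ANOVA | not applicable |

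With two visits, Friedman reduces to a sign-type test within each arm. That is all that section 2.7 leaves for the FGA.

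**The case against.** The strongest reply is that section 2.7 keeps the two purposes apart: Friedman and Dunn for change within an arm, Mann-Whitney for the difference between arms. The stated aim is comparative, and nothing says that within-arm p-values will be compared or read as efficacy. How they are interpreted, and how the FGA is handled in detail, could be settled in an analysis plan that is not shown.

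Much of this stands. A reader might infer three stronger points that the document does not support:

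- **That all these within-arm tests are bound to be positive.** This is shown only for BBS, and only for the omnibus test and the pairs with T0. The T1-T2 pair ran from 0% to over 99% in the simulations. The other ordinal outcomes come with no figures.
- **That a sub-acute effect could be shown only by setting within-arm p-values side by side.** For ordinal outcomes with a baseline, the T2 − T0 test compares the arms at T2, although it does not isolate T1 to T2. TUG and posturography have an ANOVA with time and group.
- **That the primary analysis is invalid.** BBS from T0 to T1 has a randomised between-arm test.

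The objection does not reach the FGA. The article does not leave its between-arm method open. It fixes one rule for ordinal outcomes, names the FGA among them, and elsewhere withholds the T0 value that the rule needs. That is a contradiction within the document, not a detail left to another one.

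**Conclusion.** The point holds in limited form. For ordinal outcomes the only T1-to-T2 test is within-arm, and it cannot show a treatment effect. For the FGA, EQ-5D-3L and SINGER, no planned between-arm variable can be formed and the three-visit Friedman test cannot be run as written. This defeats the stated reason for including the FGA. Both conclusions follow from the text alone.

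The near-certain significance of the within-arm BBS tests involving T0 rests on the pilot control gain of 13.67 points and survives the SD inflation. The one-arm-only rate for T1 to T2 is between about 0% and 50%. It is low for small or very large gains and high in between, and the documents do not say where the trial will fall. It measures the risk if within-arm results were compared. It is not an error rate of a test that the plan announces.

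The plan should be changed before analysis. The primary comparison is unaffected.

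**What to change.** In section 2.7:

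1. Report within-arm recovery as medians and interquartile ranges at each visit. If the Friedman and Dunn tests are kept, label them as describing change over time and not as evidence of a treatment effect.
2. State that every claim about treatment, including the sub-acute phase, rests on a between-arm comparison.
3. For the FGA, EQ-5D-3L and SINGER, compare the arms on the values at T1 and at T2, in place of change scores that cannot be formed.
4. If a T2-minus-T1 contrast is wanted, make it between arms. State that T1 follows four weeks of arm-specific therapy, so it is a post-treatment starting point and is subject to the ceiling.

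In the Discussion, bring the sentence on the FGA into line with the comparison chosen.

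The cost is wording and possibly fewer tests. No data collection, visit or sample-size figure changes.

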#### 2.3.1 Inclusion criteria

People who are at least 18 years of age, who experienced an acute ischemic or hemorrhagic stroke (identified by MRI/CT), and who suffer from gait ataxia are eligible, if they score at least 1 point on the items gait, stance, trunk or heel-shin-slide of the Scale for the Assessment and Rating of Ataxia (SARA; Schmitz-Hübsch et al., 2006) and 47 points or less on the Berg Balance Scale (BBS; Stevenson, 2001).

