#### 2.3.3 Randomization, allocation, and blinding

Participants are randomly allocated into one of two groups. Group allocation uses a 1:1 ratio to either control group (CG) or intervention group (IG) utilizing stratified blocked randomization and hidden block sizes. The allocation sequence is generated using an online randomization software (Sealed Envelope Ltd., London, UK; Sealed Envelope Ltd., 2022). Stratification variables are age (≤ 70 years, >70 years) and gender (male, female).

Allocation concealment is conducted, as an independent researcher in charge for the randomization does not disclose patients' group allocation until after the baseline assessment (T0). To effectively conceal the randomization sequence, sequentially numbered, opaque sealed envelopes are used. After T0 assessment, department staff who are independent of assessment and intervention assign the patient to the appropriate group using the sealed envelopes. The staff then informs the therapist responsible for providing the assigned intervention.

Outcome assessors are blinded to patients' group assignment. Patients are informed that an examination of the effects of two distinct physiotherapy exercise programs is performed. However, they remain unaware of the precise details of the interventions of both groups and the study's rationale. Patients are encouraged not to talk to the assessor about the exercises. The planned time for regular unblinding is after study completion.

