#### 2.5.1 Primary outcome

The primary outcome is balance as assessed using the BBS (Berg et al., 1989). The BBS is considered the gold standard for evaluating balance in people after stroke (Blum and Korner-Bitensky, 2008). It comprises 14 items, and a Likert scale is used ranging from 0 to 4, depending on the patient's performance (Table 3).

**Table 3 T3:** Outcomes, assessments, and timepoints.

**Outcome**	**Assessment**	**T0^a^**	**T1^b^**	**T2^c^**

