### 2.6 Sample size calculation

The sample size was estimated using the primary outcome data obtained from a pilot study (*n* = 7) conducted for this RCT (Meier et al., 2021), taking into account a correction for small samples. Based on a mean change in BBS score of 17.33 points (SD 2.08) in the IG and 13.67 points (SD 4.73) in the CG, the mean between-group difference and pooled SD were calculated and a correction for small samples was applied (pooled SD^*^1.442; Vickers, 2003). Using an independent samples *t*-test, power of 0.8, alpha of 0.05 and 1:1 allocation ratio, a sample size of 66 participants, 33 per group, was evaluated (HyLown Consulting LLC, 2022). Considering an attrition rate of 15%, the aim is to include 77 participants.

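### The primary BBS comparison is a valid rank test on change scores, but it adjusts for neither baseline BBS nor the randomisation strata and so gives up power and precision

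*Protocol article*

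**What the plan says.** Section 2.5.1 names the endpoint: "The primary outcome is balance as assessed using the BBS". Section 2.7 puts BBS in the ordinal class: "Medians (interquartile range) are reported for ordinal data (mRS, BBS, FGA, TCT, FES-I, FRT, EQ-5D-3L, SARA, and SINGER". Ordinal outcomes are compared between groups by a Mann-Whitney U test on differences from baseline: "To examine between-group differences, using newly created variables (T1 or T2 minus T0 values". No covariate is named for that test.

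A separate route serves the other data type: "For continuous data, test assumptions for a repeated-measures analysis of variance (ANOVA) are checked". Only that repeated-measures model is "adjusted for the stratification variables (age, sex". The outcomes listed as continuous are TUG and posturography.

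Randomisation was stratified (section 2.3.3): "Stratification variables are age (≤ 70 years, >70 years) and gender (male, female". Section 2.6 sizes the trial with an independent-samples t-test on mean BBS change, for which "the mean between-group difference and pooled SD were calculated". Section 3 says that the main objective concerns T0 to T1 and concedes a potential ceiling effect on the scale.

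**The concern.** The primary outcome gets a less efficient between-group analysis than the continuous secondary ones. Two pieces of baseline information held on every patient, T0 BBS and the stratum, are not used as covariates in the comparison that decides the trial.

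The change score does use baseline, but in a rigid way: subtraction assumes that each extra point at T0 carries over as a full point at T1. If the true slope is below 1, that over-corrects, and an arm that happens to start higher is penalised.

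The documents point to a slope below 1. BBS has 14 items scored 0 to 4, so its maximum is 14 × 4 = 56. Entry is open to patients with "47 points or less on the Berg Balance Scale". A patient entering at 47 can gain at most 56 − 47 = 9 points. The pilot's mean gain in the intervention group, 17.33, is out of reach for anyone starting above 38, because 56 − 17.33 = 38.67. Change is therefore likely to depend on the starting score.

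At stake are power and precision in a trial planned at only 80% power, and the sensitivity of the estimate to chance imbalance at T0.

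**Working it through.** **Inputs.** From section 2.6: mean changes 17.33 (SD 2.08) and 13.67 (SD 4.73), SD multiplier 1.442, power 0.80, alpha 0.05, 33 per group. From section 2.7: two-sided testing. Assumed, because the documents do not give them: the T0–T1 correlation of BBS (rho, taken from 0.3 to 0.9), equal variance at T0 and T1, normality, and the share of change variance explained by the strata (R²).

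**1. The plan's own figure.**
- Difference: 17.33 − 13.67 = 3.66.
- Pooled SD with equal weights: √[(2.08² + 4.73²)/2] = 3.654. Inflated: 3.654 × 1.442 = 5.27.
- Standardised effect d = 3.66/5.27 = 0.695.
- n per group = 2(1.96 + 0.8416)²/d² = 32.5, so 33 per group and 66 in all, as stated.
- Power of the t-test at 33 per group: 0.806 by normal approximation, 0.794 by the exact t.

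**2. The planned test.** Under normality the Mann-Whitney test has asymptotic relative efficiency 3/π = 0.955 against the t-test. Using d√0.955 in the exact t calculation gives power of about 0.77 at 33 per group. Simulation gives 0.77 to 0.78. About 35 per group would be needed for 80%.

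**3. Baseline-adjusted ANCOVA.** With T0 and T1 SD both equal to s, change variance is 2s²(1 − rho) and ANCOVA residual variance is s²(1 − rho²). Their ratio is (1 + rho)/2. Power is from the t distribution with effect d/√[(1 + rho)/2].

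**4. Effect of chance imbalance.** With equal variances the slope of T1 on T0 is rho, so an imbalance of D points at T0 shifts the change contrast by (rho − 1)D. To keep the change SD at 5.27, the baseline SD must be 5.27/√[2(1 − rho)], and the standard error of the T0 difference is that SD × √(2/33).

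| rho | variance ratio | ANCOVA power, 33 per group | n per group for 80% | implied T0 SD | SE of T0 difference | shift at 1 SE, points | % of 3.66 |
|---|---|---|---|---|---|---|---|
| 0.3 | 0.65 | 0.93 | 22 | 4.45 | 1.10 | 0.77 | 21 |
| 0.5 | 0.75 | 0.89 | 25 | 5.27 | 1.30 | 0.65 | 18 |
| 0.7 | 0.85 | 0.85 | 28 | 6.80 | 1.67 | 0.50 | 14 |
| 0.8 | 0.90 | 0.83 | 30 | 8.33 | 2.05 | 0.41 | 11 |
| 0.9 | 0.95 | 0.81 | 31 | 11.78 | 2.90 | 0.29 | 8 |

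The n column uses the normal approximation of step 1. Simulated ANCOVA power was 0.93, 0.90, 0.85 and 0.83 at rho 0.3, 0.5, 0.7 and 0.8, in agreement.

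**5. Validity.** In simulation with no treatment effect, the Mann-Whitney rejection rate was 0.046 to 0.048.

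**6. The strata.** Normal approximation for a mean comparison: with R² = 0.05, omitting the strata gives type I error 0.044, and power is 0.812 unadjusted against 0.825 adjusted. With R² = 0.10 the figures are 0.039, 0.818 and 0.845.

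**The case against.** The best defence is that a rank test on an ordinal scale is a legitimate, prespecified choice, and that the size of the gain from ANCOVA rests on a correlation the documents do not give. Both points stand. If rho is near 0.9 the gain is only about four percentage points of power. The 3/π penalty also assumes normality, which a ceiling would disturb, and it costs only about two points in any case (0.79 to 0.77). What survives is the direction: ANCOVA is ahead at every rho examined. The ordinal argument does not rule out adjustment either, since a proportional-odds model takes the same covariates, and subtracting T0 from T1 already treats BBS points as equally spaced.

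Several stronger readings are tempting and are not supported.
- A reader might infer that the plan ignores baseline BBS or leaves imbalance wholly uncorrected. It does not: T0 is subtracted, so the fault is over-correction.
- A reader might infer that the test is invalid or that omitting the strata inflates type I error. Randomisation protects the test, and omitting the strata makes it slightly conservative.
- A reader might combine a baseline SD of 10 with a slope of 0.6 and arrive at a shift of about 1 point. Under equal variances those values imply a change SD of 10 × √0.8 = 8.94, not 5.27. With SD 10 and 5.27 together, rho is 0.86 and the shift is 0.34 points.
- A reader might infer that only a p-value will be reported. The article is silent on a location-shift estimate with its interval, and that detail may sit in the full protocol or analysis plan.

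On timing, section 4 plans completion by the end of June 2024 and section 2.3.3 plans unblinding after completion, while the article is dated 5 August 2024. Whether unblinding has taken place is not stated. The change is clean only if it has not.

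**Conclusion.** The point holds as a matter of efficiency. The primary comparison is fixed in the text as unadjusted, and it can be expected to have about 0.77 power where a baseline-adjusted analysis of the same patients would have 0.81 to 0.93. Those figures rest on the planned effect and SD, 33 evaluable patients per group, normality, equal T0 and T1 variance and an assumed rho of 0.9 to 0.3. Over the same range, the conditional shift from a one-standard-error imbalance is modest. Most of the gain comes from T0 BBS. Age and sex add little unless they are strongly prognostic, though adjusting for them would match the design and the plan's own treatment of its continuous outcomes. It is a free or cheap improvement, and the planned result would not be wrong without it.

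**What to change.** Before unblinding, amend section 2.7 so that the primary analysis is an ANCOVA of T1 BBS on group, T0 BBS, age stratum (70 or younger, over 70) and sex, with robust or bootstrap standard errors, reported as an adjusted mean difference with 95% confidence interval. That estimate can be set directly against the 3.66 points used for sizing. If the ordinal view is to be kept, specify a proportional-odds model with the same covariates instead. Retain the Mann-Whitney test on change as a sensitivity analysis.

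The cost is a wording change with no new data. The small downside is that ANCOVA treats BBS as interval-scaled, as the sample size calculation in section 2.6 already does. If unblinding has already happened, the planned test should remain primary and the adjusted model should be presented as supplementary and labelled as added afterwards.
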